### Primary and secondary outcomes

Primary outcome will be infarct size, which will be measured with CMR at 6 and 84 days (12 weeks) after PCA. Both determination and data obtained by these procedures will be evaluated by two blinded independent individuals with the purpose of applying the concordance kappa index.

As our primary outcome is fully dependent on a high-quality blood-flow restoration to the ischemic myocardium region, we established as our criteria for successful reperfusion only patients who have a starting TIMI flow of 0 in the PCA and finish the procedure with TIMI flow 3, according to the most rigorous literature standards [77-79]. Secondary outcomes will be myocardial-damage biomarkers, oxidative stress- and inflammation-related biomarkers, and ejection fraction.

1. Ejection fraction: will be measured with cardiac magnetic resonance (CMR) at 6 and 84 days (12 weeks) after PCA. Both determination and data obtained by these procedures will be evaluated by two blinded independent individuals with the purpose of applying the concordance kappa index.

2. Oxidative stress-related biomarkers:

Plasma protein carbonylation

Antioxidant capacity of plasma: Ferric reducing ability of plasma (FRAP)

Plasma concentration of vitamins C and E

Thiol index: GSH/GSSG ratio in erythrocytes

Lipid peroxidation: F2-isoprostane and malondialdehyde levels in plasma and erythrocytes, respectively, will be measured.

3. Inflammation biomarkers:

High-sensitivity C-reactive protein

Leukocyte count by standard method

4. Myocardial-damage biomarkers:

Troponin, CK, and CK-MB will be measured in plasma with standard methods

Oxidative stress- and inflammation-related biomarkers and myocardial-damage biomarkers will be assessed through antecubital venous blood extraction, at the moment of enrollment (30 to 60 minutes before PCA), immediately after successful reperfusion, at 6 to 8 hours after finishing the revascularization process and before discharge, as previously described. The samples will be collected in chilled vacutainers containing disodium EDTA (final concentration, 4 m*M*) and centrifuged at 3,000 *g* for 10 minutes to separate the plasma from figurate elements. Erythrocytes will be subjected to hypotonic hemolysis by dilution with distilled water. Plasma and red blood cell lysates will be stored at -80°C until performing the biochemical analyses.

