### Sample size

Taking into account that until 50% infarct size is due to reperfusion damage, a minimal efficacy of the intervention is considered to reach a relative improvement up to 25% infarct size. Similar studies applying the same method have provided the accuracy of measurements as variance value. The sample size was calculated from the following formula [76]:

$$n=2{\left(\mathrm{ZS}+\mathrm{ZP}\right)}^{2}x\;S^{2}/{\left(\mathrm{MA}–\mathrm{MB}\right)}^{2}$$

Where *n* is the sample size for each group, “ZS” corresponds to the level of significance (5%), “ZP” represents the potency (80%), “MA” is the mean of supplemented group,MB, the mean of the placebo group (control), and S is the variance of CMR determination for assessment for IS. A 10% patient loss was considered for the purposes of this calculation. This calculation rendered a sample size of 66 patients for each branch (placebo and supplemented). This sample size is suitable to be covered by the population of patients being treated for PCA in the Cardiovascular Department, University of Chile Clinical Hospital, and Cardiovascular Center, San Borja Arriarán Clinical Hospital, during the estimated period (3 years).

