### Interventions

All patients will be asked to sign the informed consent before beginning the protocol. For those patients allocated to receive vitamin treatment, the intervention will be started as soon as the patient has signed the informed consent. The protocol will be started by administering an unique oral dose of vitamin E as α-tocopherol (800 IU) and an intravenous infusion of vitamin C as sodium ascorbate (320 m*M*) infused at a 10-ml/min flow rate during the initial hour and at 3 ml/min rate during the following 2 hours. Percutaneous coronary angioplasty will be performed about 30 minutes after initiating the vitamin C infusion. Oral doses of vitamin E (400 IU/day) and vitamin C (500 mg/12 hours) will be taken by the patients for 84 days after PCA.

For those patients allocated to receive placebo treatment, the 800-IU oral dose of vitamin E will be replaced for two vegetable oil capsules (400 mg each). The intravenous infusion of vitamin C will be replaced by an equal sodium chloride solution volume having the same osmolality as the vitamin C infusion administered to supplemented patients. The 400-IU oral doses of vitamin E will be replaced by vegetable oil (400 mg), and oral doses of vitamin C will be replaced with inert starch microgranules (500 mg). The pharmaceutical forms of vitamin C and E are indistinguishable from their respective placebos.

After the initial evaluation, patients will go to the catheterization laboratory. According to the standard protocol in AMI, an angiography will be performed to identify the infarct-related artery. The location and extent of AMI (number of arteries involved), percentage of stenosis, TIMI flow, type of stent, and so on, will be recorded. Immediately before coronary arteriography to confirm total occlusion of one coronary artery, a basal blood sample will be drawn from the antecubital vein. Three more blood samples will be obtained: immediately after successful reperfusion, at 6 to 8 hours after finishing the revascularization process and before hospital discharge.

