Infarct size, the primary endpoint of the study, will be measured with cardiac magnetic resonance (CMR) at 6 and 84 days (12 weeks) after PCA. Both determination and data obtained by these procedures will be evaluated by two independent individuals with the purpose of applying the concordance kappa index. Adherence to oral intake of vitamins C and E or placebo will be evaluated by telephonic contact effectuated weekly by the nurse responsible for the trial patient´s care.

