### Statistical analyses

Results of continuous variables will be expressed as mean ± standard deviation (SD). Comparison between parametric variables will be performed by using Student *t* test for unpaired samples. Nonparametric variables will be expressed as median (interquartile range) and compared through Wilcoxonrank-sum test. The significant differences for normally distributed variables will be compared with Student *t* test analysis of variance (ANOVA) for repeated measures. The significant differences for non-normally distributed variables will be compared by using the Mann–Whitney *U* test. Categoric variables will be expressed as numbers and frequencies (percentage). The Fisher Exact test with Katz approximation will be used to compare adverse-event frequencies.

Determination and data obtained for infarct size and ventricular function by cardiac resonance will be evaluated by two independent individuals with the purpose of applying the concordance kappa index. Among the limitations of using infarct size as an outcome, is that the use of final infarct size carries the risk of imbalances in baseline myocardium at risk, according to treatment group, as well as comparing different AMI locations, which may have different sensitivity to the therapy [80].

In addition to this, the groups may have variable time to reperfusion and other confounding variables that determine infarct size [81,82]. Whereas some of these difficulties may have been corrected through a careful stratification on entering the study, this option was discarded, given the small sample size of this study. We are currently considering an analysis of the data though a linear regression model, adjusted by all confounding variables, such as those mentioned before, and others present in the current literature [83]. *P*< 0.05 will be considered statistically significant. Results will be analyzed by using Stata version 8.0, Microsoft Excel,and Graphpad Prism 4.0.

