## Discussion

Given the unpredictable nature of AMI, it is not feasible to obtain a basal myocardial image of patients; however, this trial also does not include performing an “acute” imaging on admission before the PCA (again, for feasibility reasons), but rather relies on performing a CMR on the sixth day after AMI. In this context, it is impossible to distinguish reperfusion damage from ischemic damage in the same patient, based in a single “6-day after” cardiac image. It would be expected on an imaging comparison among groups that on the 6^th^ and 84^th^ days, the placebo group exhibits, on average, a greater infarct size compared with the supplemented group. Any significant reduction of infarct size in the supplemented group could be attributed only to a decrease of reperfusion damage, because full coronary ischemia would not allow the arrival of ascorbate to the postoccluded artery segment. However, it will be impossible to determine whether a significant decrease of infarct size corresponds to total or partial reduction reperfusion damage.

To the best of our knowledge, no published reports have assessed human populations with high vitamin C levels in AMI patients during the PCA procedure; therefore, it is more difficult to compare data obtained with those in the current literature. In addition, given the characteristics of the study population, trial results are not applicable to patients having a second AMI, III or IV Killip score AMI, or other conditions established in the trial-exclusion criteria. Given that this study is being performed in a mostly Chilean population, its applicability to other ethnicities is uncertain.

Concerning the loss of data or patients during the study, patients undergoing a claustrophobic reaction will not be capable of being analyzed by CMR. Furthermore, due to the ambulatory nature of the trial, a small loss of patients may occur between the day 6 CMR and day 84 CMR. Given the multicentric nature of the study, the loss of samples is possible.

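### Infarct size is primary at both day 6 and day 84 with no statement of which day decides; and crediting a day-84 reduction only to less reperfusion damage is not supported

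*Protocol article*

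**What the plan says.** **Primary outcome.** Under Primary and secondary outcomes: "Primary outcome will be infarct size, which will be measured with CMR at 6 and 84 days (12 weeks) after PCA". The Interventions section repeats it: "Infarct size, the primary endpoint of the study, will be measured with cardiac magnetic resonance (CMR) at 6 and 84 days (12 weeks) after PCA". The Abstract also gives both days. Neither is ranked above the other.

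**Threshold and tests.** Statistical analyses gives one general rule, that P below "0.05 will be considered statistically significant". It lists an unpaired t test, rank tests for non-normal data and a repeated-measures ANOVA, without saying which applies to infarct size. An adjusted linear regression is only under consideration.

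**Sample size.** One two-mean formula at 5% significance and 80% power, a relative improvement of up to 25% and 10% loss gives 66 per arm. No time point is named.

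**Interpretation.** The Discussion expects larger infarcts on placebo on both days, and continues: "Any significant reduction of infarct size in the supplemented group could be attributed only to a decrease of reperfusion damage". The reason given is that ascorbate cannot pass a fully occluded artery.

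**Treatment between the scans.** Interventions: "Oral doses of vitamin E (400 IU/day) and vitamin C (500 mg/12 hours) will be taken by the patients for 84 days after PCA".

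**The concern.** There are two separate problems.

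*Which day decides.* The time point is part of the definition of a primary outcome. Here two are given, with one threshold and no rule for combining them. A reader cannot tell what a positive trial would be, and nothing prevents a claim based on whichever day reaches significance. In that case the error rate exceeds the 5% used for the sample size.

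*What a day-84 difference means.* The reason given for the attribution excludes only an effect before the artery opens. It does not exclude effects in the following 12 weeks, while the active arm is still taking vitamins. A difference that appeared only at day 84 could be reported as protection from reperfusion injury, although the design cannot separate that from the effect of continued oral treatment.

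**Working it through.** **1. The protocol's own figure.** The formula is n = 2(z_α + z_β)² S² / (MA − MB)². The article gives no numbers for MA, MB or S, so 66 per arm cannot be reproduced directly. It can be solved backwards:

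- Evaluable patients per arm: 59 / 0.90 = 65.6, rounded up to 66; or 60 × 1.10 = 66. So 59 to 60.
- Implied standardised effect, taking 5% as two-sided (the article does not say): (1.960 + 0.842) × √(2/60) = 0.51 SD; with 59 per arm, 0.52 SD.
- For a 25% relative reduction, the SD is 0.25 / 0.51, about 0.49 of the control mean.

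The figure is internally plausible as the size for one comparison at 5%. It makes no allowance for a second.

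**2. Error rate if either day may be claimed.** Under no effect, let Z₁ and Z₂ be the day-6 and day-84 test statistics, bivariate normal with correlation ρ. Then

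P(at least one significant) = 1 − P(|Z₁| < 1.96 and |Z₂| < 1.96).

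The article gives no ρ, so it is an assumption shown over a range. At ρ = 0 the result is 1 − 0.95² = 0.0975.

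| ρ (assumed) | Two-sided, either day | False finding of benefit, either day |
|---|---|---|
| 0 | 9.75% | 4.9% |
| 0.5 | 9.1% | 4.5% |
| 0.7 | 8.3% | 4.2% |
| 0.8 | 7.8% | 3.9% |
| 0.9 | 7.0% | 3.5% |
| 0.95 | 6.5% | 3.2% |
| 1 | 5.0% | 2.5% |

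The nominal values are 5% and 2.5%. The rate returns to nominal only at ρ = 1.

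**3. What each possible rule costs**, at 0.51 SD and 60 evaluable per arm, assuming the same effect on both days:

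- One named day, or a fixed sequence with each test at 0.05: error at most 5%, and power for the first day stays at 80%.
- Bonferroni split, 0.025 per day: power for each day falls to 71%. Restoring 80% needs 73 evaluable per arm, and 73 / 0.90 = 81.1, so 82 recruited.
- Both days required at 0.05: error at most 5%, joint power about 69% (ρ = 0.5) to 76% (ρ = 0.95).

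**4. The attribution sentence beside the rest of the article.**

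- The Discussion argues that ascorbate cannot reach tissue beyond a complete occlusion. This concerns the period before reperfusion.
- Interventions continues oral vitamins C and E through day 84, the day of the second scan.
- Background says antioxidants may attenuate left ventricular remodelling after infarction, and that vitamin C may have some benefit through properties other than scavenging.

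The article's own rationale therefore leaves open routes other than reperfusion protection by day 84.

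**The case against.** **Testing each day at 0.05 is not written down.** A reader might infer that each day is tested separately and that either may win. The article gives a general threshold, names a repeated-measures ANOVA and expects a difference on both days. A single group test across days, or a both-days rule, would hold 5%. This stands: the inflation is conditional. It does not remove the point, because the ANOVA is tied to no outcome or contrast, the tests offered for non-normal data compare the arms at one time, and no joint rule is stated.

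**Multiplicity may be handled in an analysis plan that is not shown.** Fair for the details. But the article itself fixes the primary outcome, and fixes it as two days.

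**The attribution sentence does not raise the type I error.** Correct. It is a statement about mechanism, and it speaks of a significant reduction in the supplemented group, not of any difference. It is a separate point from the error rate.

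**Oral vitamin C is not expected to work.** Background says that oral dosing should not be expected to prevent oxidative damage in ischemia-reperfusion. That weakens the alternative explanation, but the same section allows other beneficial properties, and vitamin E is also given. The remodelling remark concerns dilation more than infarct size. This is enough to defeat *only*, though not to show that oral treatment has an effect.

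**Imbalance in myocardium at risk.** The article concedes that "the use of final infarct size carries the risk of imbalances in baseline myocardium at risk". A reader might add this to the case. Chance imbalance under randomisation does not inflate the error rate and is not specific to day 84, so it adds nothing here.

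**It is a pilot.** True, and large-scale replication is foreseen. But its first stated objective is efficacy on infarct size, and it is sized for that.

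**Conclusion.** The concern holds in two limited parts.

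First, the primary outcome is fixed at two days with no deciding day or rule, and the sample size is tied to neither. If either day may carry the claim, the two-sided false-positive rate is about 7.0% to 8.3% for assumed correlations of 0.9 to 0.7, and 6.5% to 9.75% over 0.95 to 0. This rests on two-sided tests at 0.05 on each day and on an assumed correlation. The documents do not support saying that the trial's error rate does exceed 5%, because a rule that holds it has been neither stated nor excluded.

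Second, attributing a day-84 reduction solely to less reperfusion damage is unsupported. A reader might go further and conclude that no day-84 claim could stand. That is too strong: day 84 is a randomised, blinded comparison and can support an effect of the whole regimen, subject to the multiplicity question and to losses after day 6.

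**What to change.** Before unblinding:

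1. Name one deciding time point for infarct size and state that the sample size refers to it. Day 6 is a reasonable choice: it is closest to the hypothesis about the infusion around angioplasty, and it precedes the losses that the Discussion expects between the two scans. It is not a pure test of the infusion, because some oral dosing comes before it. Choosing day 84, or a joint or both-days rule, would also control the error, with the power consequences shown above.
2. Test the other day only if the first is significant (fixed sequence, each at 0.05), or make it secondary.
3. State which of the listed tests is the primary analysis of infarct size.
4. Limit the attribution sentence in the Discussion so that a day-84 difference is read as the effect of the full infusion-plus-oral regimen.

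The cost is wording only, with no extra patients and no loss of power on the deciding day. Trial status reports 43 patients enrolled, of 132 (2 × 66) or 134 (Abstract) planned, with the trial scheduled to end in March 2016. The downside, if day 6 is chosen, is that a difference seen only at day 84 could no longer be called a positive primary result.

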### Statistical analyses

Results of continuous variables will be expressed as mean ± standard deviation (SD). Comparison between parametric variables will be performed by using Student *t* test for unpaired samples. Nonparametric variables will be expressed as median (interquartile range) and compared through Wilcoxonrank-sum test. The significant differences for normally distributed variables will be compared with Student *t* test analysis of variance (ANOVA) for repeated measures. The significant differences for non-normally distributed variables will be compared by using the Mann–Whitney *U* test. Categoric variables will be expressed as numbers and frequencies (percentage). The Fisher Exact test with Katz approximation will be used to compare adverse-event frequencies.

Determination and data obtained for infarct size and ventricular function by cardiac resonance will be evaluated by two independent individuals with the purpose of applying the concordance kappa index. Among the limitations of using infarct size as an outcome, is that the use of final infarct size carries the risk of imbalances in baseline myocardium at risk, according to treatment group, as well as comparing different AMI locations, which may have different sensitivity to the therapy [80].

In addition to this, the groups may have variable time to reperfusion and other confounding variables that determine infarct size [81,82]. Whereas some of these difficulties may have been corrected through a careful stratification on entering the study, this option was discarded, given the small sample size of this study. We are currently considering an analysis of the data though a linear regression model, adjusted by all confounding variables, such as those mentioned before, and others present in the current literature [83]. *P*< 0.05 will be considered statistically significant. Results will be analyzed by using Stata version 8.0, Microsoft Excel,and Graphpad Prism 4.0.

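### Four-sample biomarkers: overlapping tests chosen by distribution, and no baseline-adjusted or arm-by-time comparison fixed

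*Protocol article*

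**What the plan says.** The section on primary and secondary outcomes schedules the blood samples "at the moment of enrollment (30 to 60 minutes before PCA), immediately after successful reperfusion, at 6 to 8 hours after finishing the revascularization process", with a fourth before discharge. It covers oxidative-stress, inflammation and myocardial-damage markers.

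The Statistical analyses section gives general rules for continuous variables and does not name the biomarkers, but they fall under these rules:

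- For parametric variables: "Comparison between parametric variables will be performed by using Student" t test for unpaired samples.
- For the rest: "Nonparametric variables will be expressed as median (interquartile range) and compared through Wilcoxonrank-sum test".
- Then, for normally distributed variables, a phrase that joins the t test to "analysis of variance (ANOVA) for repeated measures".
- Then, for non-normal variables: "The significant differences for non-normally distributed variables will be compared by using the Mann–Whitney" U test.

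The only mention of covariate adjustment is tentative: "We are currently considering an analysis of the data though a linear regression model, adjusted by all confounding variables". It follows a discussion of what determines infarct size, and baseline biomarker values are not mentioned.

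The Discussion expects some missing data: "Given the multicentric nature of the study, the loss of samples is possible", and "a small loss of patients may occur between the day 6 CMR and day 84 CMR".

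**The concern.** A normal marker has two candidate methods and no rule for choosing between them. If the ANOVA is used, no contrast is named: the group main effect and the group-by-time interaction answer different questions and can disagree. A non-normal marker has one two-sample rank test under two names. It takes one value per patient, so it can compare the arms at one time but cannot analyse four correlated values together. Troponin, CK, C-reactive protein and F2-isoprostane may well be skewed, so this could affect much of the secondary outcome set.

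In neither branch is the enrolment value used as a covariate. Precision is therefore given up in a trial that calls its own sample small, and the choice of contrast stays open until the data are seen.

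**Working it through.** **Inputs from the document.** Four samples per patient; 66 per arm including 10% loss (Sample size), so 66 × 0.9 = 59.4, taken as 60 evaluable per arm; 5% significance. The article prints no sizing figure for the biomarkers. The 66 concerns infarct size and cannot be reproduced, because the means and the variance are not printed. It matters here only as the number of patients.

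**Assumed inputs.** Two-sided testing; a treatment effect of 0.5 SD; baseline-to-follow-up correlation ρ of 0.3, 0.5 or 0.7; loss per sample of 2%, 5% or 10%. None of these is in the document.

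**Step 1: precision at one post-baseline time.** Adjusting for baseline multiplies residual variance by 1 − ρ². Power is about Φ(0.5 × √(60/2) / √(1 − ρ²) − 1.96), where 0.5 × √30 = 2.739.

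| Comparison | Variance factor | 2.739/√factor | Power |
|---|---|---|---|
| Follow-up value only | 1 | 2.739 | 78% |
| Adjusted, ρ = 0.3 | 0.91 | 2.871 | 82% |
| Adjusted, ρ = 0.5 | 0.75 | 3.162 | 88.5% |
| Adjusted, ρ = 0.7 | 0.51 | 3.835 | 97% |

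**Step 2: dilution in the repeated-measures ANOVA.** Take ρ = 0.5 between all pairs of times and an effect of 0, 0.5, 0.5, 0.5 SD at the four samples.

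- Group main effect: mean effect 1.5/4 = 0.375; variance of a patient's four-sample mean (1 + 3 × 0.5)/4 = 0.625; 0.375/√0.625 × √30 = 2.598; power Φ(0.638) = 74%. A simulation of 4,000 runs gave 72%.
- Group-by-time interaction: 81% in the same simulation.
- Mean of the three post-baseline values, unadjusted: variance (1 + 2 × 0.5)/3 = 0.667; 0.5/√0.667 × √30 = 3.354; power 92%.
- The same mean adjusted for baseline: variance 0.667 − 0.5² = 0.417; 0.5/√0.417 × √30 = 4.243; power 99%.

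**Step 3: chance baseline imbalance, with no treatment effect.** The simulation imposed a 0.3 SD shift in full at all four times. The main effect was then significant in 55% of runs and the interaction in 5.5%.

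That case is severe. The standard error of a baseline difference is √(2/60) = 0.183, so 0.3 is 1.64 standard errors, reached in about 10% of randomisations. With ρ = 0.5 only 0.15 of the 0.3 is expected to persist. The mean shift is then (0.3 + 3 × 0.15)/4 = 0.1875, the critical value is 1.96 × √(0.625 × 2/60) = 0.283, and the conditional SD is √(9/16 × 0.417 × 2/60) = 0.0884. Rejection is about Φ(−(0.283 − 0.1875)/0.0884) = Φ(−1.08) = 14%. Over all randomisations the rate stays nominal (4.9% simulated).

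**Step 4: completeness, only if a classical complete-case ANOVA were used.** With independent loss p per sample, the share of patients with all four samples is (1 − p)⁴: 0.98⁴ = 92.2%, 0.95⁴ = 81.5%, 0.90⁴ = 65.6%. Of 132 patients that is about 122, 108 and 87.

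**Step 5: is the first sample a baseline?** The outcomes section places it at enrolment, 30 to 60 minutes before angioplasty. The Interventions section places the basal sample just before arteriography, and has the infusion start on consent with angioplasty about 30 minutes later. On the second description the infusion may already be running when the sample is drawn.

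**The case against.** The strongest reply is that this is imprecise wording about secondary outcomes in a self-described pilot, and that contrasts and missing-data rules belong in an analysis plan that is not shown. The objectives ask for marker levels at stated times, and a rank or t test between randomised arms at each time answers that validly. The two later sentences on tests may only repeat the earlier two. The gains rest on assumed correlations: at ρ = 0.3 the variance falls by only 9%, and at zero by nothing.

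Much of this stands. It rules out three stronger readings that a reader might infer:

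- *That baseline is unused.* This is true of t and rank tests on post-baseline values. A repeated-measures ANOVA over all four samples includes baseline as a time level, and its interaction reflects change from it.
- *That incomplete patients are dropped.* The article says this nowhere. It would follow only from a classical complete-case ANOVA; the single-time tests use every value available at that time.
- *That skewed markers get no valid analysis.* They get a valid comparison at each time. What they lack is one that uses the repeated structure and the baseline.

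The reply does not remove the point. What is criticised is what the article states: two methods for the same variables without a rule, and one test under two names.

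**Conclusion.** The point holds for the biomarker outcomes and should be fixed. It concerns precision and pre-specification; the planned single-time tests are not invalid. The overlap between methods and the unnamed contrast are on the face of the text and need no assumption.

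The size is illustrative. Against a follow-up-only comparison, the variance falls by 9%, 25% or 49% at ρ = 0.3, 0.5 or 0.7. Against the ANOVA main effect, the cost is dilution (0.375 in place of 0.5 SD in the example) and sensitivity to the baseline imbalance that happens to occur; the overall type I error is not inflated. The completeness figures apply only if a complete-case ANOVA is chosen. The whole gain depends on the first sample being truly pre-infusion, which the article leaves unsettled.

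**What to change.** First reconcile the Interventions section with the outcomes section on when the first sample is drawn relative to the start of the infusion. Adjust only for a value confirmed to be pre-infusion, since adjusting for a later one could remove part of the treatment effect.

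Then replace the overlapping tests for the biomarkers with one pre-specified analysis per marker:

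- a linear mixed model of the three post-baseline values, on the log scale where the marker is skewed, with the scale fixed in advance;
- terms for arm, time, arm × time, baseline value, baseline × time and centre, with within-patient correlation modelled;
- the arm difference, or ratio on the log scale, with 95% confidence interval at each post-baseline time;
- rank tests at each time as sensitivity analyses, under one name.

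This model keeps patients who miss one post-baseline sample, under a missing-at-random assumption. The same type of model without a baseline term could serve infarct size and ejection fraction at days 6 and 84, but that is optional.

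The cost is a paragraph of wording and standard mixed-model code, after checking that the chosen software release can fit the model. No extra patients, samples or visits are needed.

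### Reader agreement on infarct size and ejection fraction, both continuous, is to be measured with kappa without categories or weights, so the reported reproducibility will depend on an unstated grouping

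*Protocol article*

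**What the plan says.** The protocol article names kappa as the reader-agreement statistic four times:

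- **Interventions**, for infarct size: the CMR determinations and data "will be evaluated by two independent individuals with the purpose of applying the concordance kappa index".
- **Primary and secondary outcomes**, for infarct size: they "will be evaluated by two blinded independent individuals with the purpose of applying the concordance kappa index".
- **Primary and secondary outcomes**, item 1: the same sentence is repeated after "Ejection fraction: will be measured with cardiac magnetic resonance (CMR) at 6 and 84 days (12 weeks) after PCA".
- **Statistical analyses**, for infarct size and ventricular function: data obtained "by cardiac resonance will be evaluated by two independent individuals with the purpose of applying the concordance kappa index".

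None of these places defines classes of infarct size or ejection fraction, or names a weighting scheme. No other agreement measure appears in the article.

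Elsewhere infarct size is a continuous quantity. The Sample size section works from group means and a variance: "the mean of the placebo group (control), and S is the variance of CMR determination for assessment for IS". The Statistical analyses section adds: "We are currently considering an analysis of the data though a linear regression model".

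**The concern.** Kappa measures how often two raters choose the same category, beyond chance. Infarct size and ejection fraction are measurements, and the article supplies no categories for them. Applied to raw values, unweighted kappa treats a difference of one unit and a difference of twenty as the same failure. Applied to grouped values, it depends on where the groups are cut.

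This is the only reader-agreement measure the article names for its primary endpoint. At stake is whether readers of the results can judge how reproducible the CMR measurement was. One pair of readers could be reported as good or poor depending on a choice the article does not fix. The figure would also give no reading error in infarct-size units, which is what one would want to set against the measurement variance that the Sample size section relies on.

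**Working it through.** The article states no agreement figure, so there is nothing to reproduce. The check asks what kappa would show for readers whose true agreement is known.

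**Inputs.** All are assumptions; the article gives none of them. Single readings are normal with mean 20 and SD 10. The true ICC is 0.95 or 0.90, so the reader-error SD is 10 × √0.05 = 2.24 or 10 × √0.10 = 3.16. For each ICC, 400,000 pairs of readings were simulated.

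**Formula.** κ = (pₒ − pₑ)/(1 − pₑ), where pₒ is the observed and pₑ the chance proportion of identical categories.

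**Two worked values at ICC 0.95.**
- One cut at 20: pₒ = 0.898 and pₑ = 0.5, so κ = 0.398/0.5 = 0.80. As a check, a cut at the mean of a bivariate normal gives κ = (2/π) × arcsin(ICC), which is 0.80 at 0.95 and 0.71 at 0.90, whatever the mean and SD.
- Values rounded to whole units: pₒ = 0.124 and pₑ ≈ 0.028, so κ ≈ 0.096/0.972 = 0.10.

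**Same readers, different grouping.**

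| Grouping | κ, ICC 0.95 | κ, ICC 0.90 |
|---|---|---|
| Cut at 20 | 0.80 | 0.71 |
| Cut at 10 | 0.77 | 0.68 |
| Cut at 40 | 0.70 | 0.58 |
| Cuts at 10, 20, 30 | 0.69 | 0.56 |
| Eight classes, 5 units wide | 0.49 | 0.35 |
| Whole units | 0.10 | 0.06 |
| Rounded to 0.1 | 0.01 | 0.006 |

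On the same readings the concordance correlation coefficient (CCC) is 0.95 and 0.90, with no grouping to choose.

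**Systematic offset.** Let one reader score 3 points higher, at ICC 0.95. Kappa falls from 0.80 to 0.72 with one cut at 20, and from 0.69 to 0.57 with cuts at 10, 20 and 30. Two readers with no offset but more random error (ICC 0.90) give 0.71 and 0.56. Kappa is therefore almost the same in both situations and cannot say which one holds.

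The CCC alone does not separate them either. With the offset it is 2 × 95/(100 + 100 + 3²) = 190/209 = 0.91, against 0.90 without offset at the lower ICC.

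Bland-Altman does separate them. The SD of the difference between readers is 10 × √(2 × (1 − ICC)), that is 3.16 at ICC 0.95 and 4.47 at 0.90. The first pair shows a bias of 3 with limits of 3 ± 1.96 × 3.16 = 3 ± 6.2. The second shows a bias of 0 with limits of 0 ± 1.96 × 4.47 = 0 ± 8.8.

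**Averaging the two readings (optional).** The variance of the mean relative to a single reading is ICC + (1 − ICC)/2. This is 0.99, 0.975 and 0.95 for ICC 0.98, 0.95 and 0.90, a reduction of 1%, 2.5% and 5%.

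**The case against.** **Weighted kappa may be meant.** Quadratic-weighted kappa on the numeric scale equals the CCC (0.95 and 0.90 in the simulation), and a condensed article may leave weights to a fuller document. For this reason kappa cannot be called meaningless in every form. But the article names no weights at any of its four mentions. If a weighted form was intended, the text still has to say so. The point is that an unsuitable statistic is named, not that detail is missing.

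**An offset does not go unseen.** A reader might infer that kappa is blind to a systematic difference between readers. That is wrong, since the offset lowers kappa in the figures above. What stands is that kappa neither isolates the offset nor measures it.

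**The trial result is not at risk.** A reader might also infer that the treatment comparison is compromised. The article does not support this. Kappa is descriptive and enters no test, and no decision in the article depends on it. The outcomes section has the scans read by "two blinded independent individuals with the purpose of applying the concordance kappa index", so a constant offset would cancel from the group difference when each reader scores both arms. This objection stands in full and limits the point to reporting.

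**The second reading is not shown to be wasted.** The article does not say which reading is analysed, or whether the two are combined. An article commonly leaves that to a fuller document, so it cannot be held against the plan.

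**Conclusion.** The concern holds in a limited form. Kappa, as named and without categories or weights, does not suit the two continuous CMR endpoints. From two groups down to whole-unit values, the figure for identical readers ranges from 0.80 to 0.10 at ICC 0.95, and from 0.71 to 0.06 at ICC 0.90.

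These values rest on the assumed normal distribution, SD and ICCs. Other assumptions would move the numbers, but not the dependence on grouping. The consequence is confined to the reported reproducibility of infarct size and ejection fraction. It is a modest fault, worth correcting because correction is nearly free.

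**What to change.** At all four mentions (Interventions; Primary and secondary outcomes, for infarct size and for ejection fraction; Statistical analyses), replace kappa with a two-way absolute-agreement ICC, or the CCC, with its 95% CI, together with Bland-Altman bias and 95% limits of agreement. The Bland-Altman part is needed because neither the ICC nor the CCC alone separates offset from random error. Suggested wording: *Inter-reader agreement for infarct size and ejection fraction at days 6 and 84 will be reported as the two-way absolute-agreement intraclass correlation coefficient with 95% CI, and as Bland-Altman mean difference and 95% limits of agreement.* This changes wording only, because both readings are already planned.

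Optionally, the mean of the two blinded readings could be the analysed value, for a 1% to 5% reduction in outcome variance over an assumed single-reader ICC of 0.98 to 0.90. That defines the analysed outcome, so it goes beyond wording and should be settled before unblinding if it is adopted.
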